## Abstract

**Background:**

Dyspnea is a prevalent symptom in individuals with hypermobile Ehlers-Danlos Syndrome (hEDS) and generalized hypermobility spectrum disorder (G-HSD), yet its contributors have not been identified. One known contributor to dyspnea is respiratory muscle weakness. The feasibility and effectiveness of inspiratory muscle training (IMT) in combination with standard-of-care rehabilitation (aerobic, resistance, neuromuscular stabilization, and balance and proprioception exercises) in improving respiratory muscle strength and patient-reported outcomes in patients with hEDS or G-HSD have not been evaluated.

**Objective:**

This study aims to evaluate dyspnea, respiratory muscle strength, and patient-reported outcome measures (PROMs) in hEDS or G-HSD compared with healthy controls and to assess the feasibility of a randomized controlled trial of IMT and standard-of-care rehabilitation for improving respiratory muscle strength, exercise capacity, and PROMs compared with standard-of-care rehabilitation in hEDS and G-HSD.

**Methods:**

The study will include 34 participants with hEDS or G-HSD and 17 healthy, age- and sex-matched controls to compare respiratory muscle structure and function and PROMs. After baseline assessments, participants with hEDS or G-HSD will be randomized into the intervention group and provided IMT combined with Ehlers-Danlos Syndrome standard-of-care rehabilitation or into the usual care group, and provided only standard-of-care rehabilitation for 8 weeks. The intervention group will be prescribed IMT in their home environment using the POWERbreathe K5 IMT device (POWERbreathe International Ltd). IMT will comprise 2 daily sessions of 30 breaths for 5 days per week, with IMT progressing from 20% to 60% of the baseline maximal inspiratory pressure (MIP) over an 8-week period. Feasibility will be assessed through rates of recruitment, attrition, adherence, adverse events, and participant satisfaction. The primary pilot outcome is MIP change over an 8-week period in hEDS or G-HSD. Secondary outcomes will include the evaluation of dyspnea using Medical Research Council Scale and 18-point qualitative dyspnea descriptors; diaphragmatic thickening fraction using ultrasound; respiratory muscle endurance; pulmonary function; prefrontal cortical activity using functional near-infrared spectroscopy; aerobic capacity during cardiopulmonary exercise testing; quality of life using Short Form-36; and scores from the Depression, Anxiety, and Stress scale-21. These measures will also be performed once in healthy controls to compare normative values. Multivariable regression will be used to assess the contributors to dyspnea. Paired 2-tailed *t* tests will be used to assess the changes in MIP and secondary measures after 8 weeks of IMT.

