### Respiratory Manifestations in EDS and G-HSD

Our research group and others have recently highlighted that respiratory manifestations are common in hEDS and G-HSD and include, but are not limited to, dyspnea, cough, asthma, and respiratory muscle weakness [2,9]. The collagen abnormalities lead to impairments throughout the respiratory system, which may contribute to the respiratory abnormalities observed in this population [2,10]. In individuals with hEDS, the prevalence of dyspnea is estimated to be approximately 50% [11]. Dyspnea has been described in a few studies on individuals with G-HSD, but its prevalence and determinants have not been well characterized [12]. A study reported that up to 26% of the patients with G-HSD presented with cardiorespiratory manifestations such as dyspnea, palpitations, and chest pain, which were commonly attributed to autonomic dysfunction [13].

Respiratory symptoms in EDS and G-HSD have also been associated with worse outcomes such as lower physical activity levels and function. Individuals with EDS or G-HSD experienced increased dyspnea while walking on a flat level compared with healthy controls [12]. Furthermore, a study investigating physical activity levels between patients with hEDS or G-HSD with autonomic dysfunction and those without autonomic dysfunction observed that autonomic dysfunction was associated with exercise intolerance, which is often attributed to increased symptoms of dyspnea and chest pain [14]. Postural orthostatic tachycardia syndrome, a more severe form of autonomic dysfunction, has also been observed to be associated with dyspnea, chest pain, and impairments in HRQL [15,16]. Thus, respiratory manifestations in individuals with hEDS or G-HSD have important consequences on exercise tolerance, HRQL, and functional abilities.

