### Study Arms

#### Overview

The participants in both the intervention and usual care groups will receive the standard-of-care rehabilitation in the GEAR program. Those in the intervention group will receive IMT in addition to the GEAR program components, as shown in Table 2.

**Table 2 table2:** Summary of the study procedures.

Study groups	IMT^a^ intervention group with participants with hEDS^b^ or G-HSD^c^ (n=17)	Usual care group with participants with hEDS or G-HSD (n=17)
Standard of care—GEAR^d^ program: baseline (T_0_), 4 weeks from T_0_ (T_1_), 8 weeks from T_0_ (T_2_), and 20 weeks from T_0_ (T_3_)	Aerobic, resistance, neuromuscular stabilization, and balance and proprioception exercises [36]	Aerobic, resistance, neuromuscular stabilization, and balance and proprioception exercises [36]
Baseline assessment (details provided in Table 1)	Baseline assessment: explanation of equipment and tracking IMT device POWERbreathe K5 IMT and exercise logs and Fitbit device and instructions Fitbit device and instructions Exercise logs	Baseline assessment: Fitbit device and instructions Exercise logs
Study intervention: 8 weeks	2 daily IMT sessions of 30 breaths (<5 minutes per session) for 5 days per week, up to 8 weeks IMT starting at 20% of MIP^e^ (up to a maximum of 60%) Intensity progressed by 5% to 10% if the median weekly Borg dyspnea score is <7 Web-based supervision by the study team Weekly check-in with the study coordinator	N/A^f^
Follow-up: week 4 time point	Study assessments will be performed at week 4 from the home environment. Exercise logs and respiratory muscle endurance will be assessed	Study assessments will be performed at week 4 from the home environment. Exercise logs and respiratory muscle endurance will be assessed
End point: week 8 time point	Study assessments conducted at baseline will be performed again at week 8 in the PFT^g^ laboratory. Collection of logs, Fitbits, and IMT device (POWERbreathe K5) will be done at the end of the study	Study assessments conducted at baseline will be performed at week 8 in the PFT laboratory. Collection of logs, Fitbits, and IMT device (POWERbreathe K5) will be done at the end of the study.

^a^IMT: inspiratory muscle training.

^b^hEDS: hypermobile Ehlers-Danlos Syndrome.

^c^G-HSD: generalized hypermobility spectrum disorder.

^d^GEAR: GoodHope Exercise and Rehabilitation Program.

^e^MIP: maximal inspiratory pressure.

^f^N/A: not applicable.

^g^PFT: pulmonary function test.

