#### Intervention Group (IMT)

The participants in the intervention group will receive an individual and personalized prescription for an IMT program for 8 weeks. This IMT program will use the POWERbreathe K5 IMT device in the participants’ home environment combined with the standard-of-care rehabilitation as part of the GEAR program, as described earlier. A research coordinator will facilitate these training sessions and monitor the participants via the web for the first 3 sessions in the first week and once a week from weeks 2 to 8. Over 8 weeks, 2 daily IMT sessions of 30 breaths (<5 min/session) will be performed for 5 days per week, starting with 20% of the participants’ T_0_ MIP up to a maximum of 60%. This protocol was developed based on the previous literature on IMT applied in lung transplant candidates at our center [70-72]. The total workload per session (product of inspiratory muscle force and inhaled volume expressed in Joules) will be abstracted from the IMT device. Additional variables abstracted from the device will include inspiratory muscle load (cm H_2_O), mean power per breath (W), and mean volume per breath (Liters).

The participants will be asked to record their resting and post-IMT Borg dyspnea scores for 5 days of the week (2 sessions per day), along with any side effects for each session. The median Borg dyspnea score for the previous week will be reviewed by the research coordinator, and IMT intensity will be increased by 5% to 10% of the T_0_ MIP if the median weekly Borg dyspnea score is <7 (very severe breathlessness with IMT) [54].

The participants will be asked to maintain IMT diaries to assess adherence. They will receive instructions and feedback on how to optimize their home training efforts based on direct observation of their IMT with the POWERbreathe K5 device and review of IMT workload from the device. They will have the possibility to schedule additional sessions with the study team during the week, if further support is needed.

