### Trial Outcomes

#### Estimates of Intervention Feasibility

Study feasibility will be assessed through recruitment rate, attrition, IMT program adherence, safety, and satisfaction (Textbox 1).

Feasibility estimates.RecruitmentWe will evaluate the recruitment rate as the number of participants who consented and enrolled relative to the total number of eligible patients approached for eligibility assessment by the research coordinator. The reasons for nonparticipation in the study will be documented. A successful recruitment rate will be defined as 20% in this study.RetentionRetention will be evaluated through participant attrition throughout the intervention period. For each arm of the study, the retention rate will be assessed by measuring the number of participants who completed all assessments compared with the number of participants who enrolled and randomized. A successful retention rate will be defined as ≥80% in this study.AdherenceAdherence to inspiratory muscle training (IMT) in the intervention group will be tracked electronically and through participant logs (number of completed sessions of 30 breaths out of 10 planned sessions per week) with the IMT device over the 8-week period. Adherence will also be assessed during weekly communications with participants as well as through completed daily IMT logs, which will capture IMT training days and IMT prescription (percentage of maximal inspiratory pressure). These data will also be verified after the IMT device is returned. The number of completed IMT sessions will be reviewed from the recordings on the device.The physical activity and exercise behaviors prescribed through the GoodHope Exercise and Rehabilitation Program will be monitored in both the intervention and usual care groups. Daily step counts will be assessed from the Fitbit device. The participants with hypermobile Ehlers-Danlos Syndrome or generalized hypermobility spectrum disorder will be asked to download the Fitbit app on their smartphones or tablets. A 1-page document highlighting the key steps for setting up the Fitbit tracker will be provided. We will also work with the participants via the web to set up the device if any problems arise. The exercise behaviors of the study participants in both groups will be reviewed using the self-reported exercise logs, which capture the exercise type, frequency, intensity, and duration on a daily basis. At the end of the baseline assessment, the study participants in both the usual care and intervention groups will be provided with documents explaining the maintenance and use of the study devices (eg, Fitbit, respiratory muscle endurance trainer, and IMT device for the intervention group).SafetyThe participants will log any adverse effects during the IMT program, which will be reviewed weekly by the research coordinator. Adverse effects are rare; however, symptoms previously observed during IMT include mild chest discomfort, worsening respiratory symptoms (eg, dyspnea), and possibly nausea related to hyperventilation [73]. The participants will also be strongly encouraged to immediately contact a member of the research team if they notice any adverse events. Study personnel will also inquire about chest discomfort or delayed-onset muscle soreness during IMT in weekly meetings to adjust IMT prescriptions and ensure tolerability of training intensity.SatisfactionParticipation satisfaction and motivation to engage with the IMT program will be assessed in the intervention group using a standardized questionnaire administered at weeks 1, 4, and 8 after study enrollment.

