### Statistical Analysis

#### Proposed Data Analyses

For objective 1, we aim to compare respiratory muscle structure and function and PROMs between patients with hEDS or G-HSD and healthy controls and to evaluate the main correlates with dyspnea in patients with hEDS or G-HSD. Descriptive statistics will be used for continuous variables (mean and SD or median and IQR), and frequencies will be used for categorical variables. We will use multivariable regression analysis to compare any differences between groups across respiratory parameters and PROMs, adjusted for EDS subtype (hEDS or G-HSD). We will explore the associations with peak Borg dyspnea scores during CPET using multivariable regression, with possible determinants being MIP, diaphragm thickening fraction, PFC activity, and PFT parameters.

For objective 2, we aim to assess the feasibility of IMT and standard-of-care rehabilitation for improving respiratory muscle strength, exercise capacity, and PROMs compared with standard-of-care rehabilitation alone in patients with hEDS or G-HSD. Descriptive statistics will be used to summarize program adherence, recruitment, participant satisfaction, attrition, and safety in the hEDS or G-HSD study groups. Estimates of within- and between-group differences at T_0_, 4 weeks, and 8 weeks will be reported using means and 95% CI. Paired *t* tests and *t* tests will be used to compare the changes in the primary pilot outcome (MIP) and secondary measures over the 8-week study period within and between the 2 randomized groups.

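### Scheduled adverse-event collection is described only for the IMT arm, so the planned safety summary cannot compare the arms or separate IMT events from background symptoms

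*Protocol article*

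**What the plan says.** The abstract's Methods section lists adverse events among the rates by which feasibility is judged: "Feasibility will be assessed through rates of recruitment, attrition, adherence, adverse events, and participant satisfaction". Under Proposed Data Analyses, objective 2, descriptive statistics will cover "attrition, and safety in the hEDS or G-HSD study groups".

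Collection is set out in three places:

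- Textbox 1, Safety: "participants will log any adverse effects during the IMT program, which will be reviewed weekly by the research coordinator", and "Study personnel will also inquire about chest discomfort or delayed-onset muscle soreness during IMT in weekly meetings".
- Intervention Group (IMT): participants record Borg scores at each session, "along with any side effects for each session".
- Table 2, study intervention row, IMT column: "Weekly check-in with the study coordinator". The usual care cell of that row is marked not applicable.

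For usual care, the week 4 entry of Table 2 reads "Exercise logs and respiratory muscle endurance will be assessed", with the same text for both arms. Textbox 1 describes the exercise log as recording type, frequency, intensity and duration. No adverse-event item is described for the log or for the week 4 and week 8 assessments. The one route not tied to IMT is the encouragement in the Safety paragraph to contact the team about any adverse event.

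**The concern.** A symptom asked about every week is recorded more often than the same symptom left to be volunteered. That matters here because the symptoms sought overlap with the disease. The Introduction reports dyspnea in about half of people with hEDS and, in up to 26% of those with G-HSD, "cardiorespiratory manifestations such as dyspnea, palpitations, and chest pain". Both arms also do aerobic and resistance exercise, which may cause soreness.

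Two things are at stake. If safety is shown for the two groups side by side, IMT will tend to look worse even if it is harmless. If it is shown for IMT alone, the reader cannot tell how much of the rate is disease or rehabilitation. Randomization supplies the comparison that would settle this, but one-arm collection gives it up. The Discussion says that the findings will inform a larger study, so a distorted safety picture would carry forward.

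**Working it through.** The protocol gives no expected adverse-event rate, safety threshold or safety sample size, so there is no figure to reproduce. The check has two parts.

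**1. Scheduled collection per participant over 8 weeks**

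| Route | IMT | Usual care |
|---|---|---|
| Side-effect entry at each session | 2 × 5 × 8 = 80 | none described |
| Weekly review of the adverse-effect log | yes | none described |
| Weekly questions on chest discomfort and soreness | yes | none described |
| Weekly check-in | yes | not applicable |
| Symptom item in exercise log, or at week 4 or 8 | none described | none described |
| Encouragement to contact the team | yes | not expressly excluded |

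**2. Illustration of what unequal collection can do**

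Both illustrations assume 17 per arm and no true IMT effect. The reporting probabilities are assumptions, not protocol figures.

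*(a) Weekly complaint rate.* Let p be the chance per participant-week of a reportable complaint, the same in both arms and independent between weeks. Let v be the share that usual care volunteers, and let IMT record everything.

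- IMT: 1 − (1 − p)^8
- Usual care: 1 − (1 − pv)^8

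For p = 5%, IMT shows 1 − 0.95^8 = 33.7%, about 6 of 17. With v = 25%, usual care shows 1 − 0.9875^8 = 9.6%, a gap of 24.1 points.

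Gap in percentage points:

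| p per week | IMT shows | v = 0 | v = 25% | v = 50% | v = 75% | v = 100% |
|---|---|---|---|---|---|---|
| 2% | 14.9% | 14.9 | 11.0 | 7.2 | 3.5 | 0 |
| 5% | 33.7% | 33.7 | 24.1 | 15.3 | 7.3 | 0 |
| 10% | 57.0% | 57.0 | 38.6 | 23.3 | 10.5 | 0 |

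*(b) The Introduction's prevalence figures as background.* Assume that IMT captures 90% of affected participants and usual care captures 60%, 30% or 10%. Expected count = 17 × background × capture. The last column is from exact binomial distributions.

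| Background | Usual care capture | IMT v usual care, of 17 | Excess (points) | Chance that IMT shows more |
|---|---|---|---|---|
| 26% | 60% | 3.98 v 2.65 | 7.8 | 64% |
| 26% | 30% | 3.98 v 1.33 | 15.6 | 85% |
| 26% | 10% | 3.98 v 0.44 | 20.8 | 96% |
| 50% | 60% | 7.65 v 5.10 | 15 | 77% |
| 50% | 30% | 7.65 v 2.55 | 30 | 96% |
| 50% | 10% | 7.65 v 0.85 | 40 | >99% |

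With 90% capture in both arms, the expected excess is 0 and IMT shows the higher count by chance in 42% (background 26%) or 43% (background 50%) of trials.

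The 50% rows rest on dyspnea, the symptom best covered by other data (see the objection). Prevalence is also not the same as the share who would report an event in 8 weeks.

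**The case against.** The strongest reply is that the Safety paragraph sits under feasibility of the intervention, beside IMT adherence and IMT satisfaction. Logging side effects in the treated arm is an ordinary tolerability measure for a small pilot and needs no control rate. The sentence that mentions study groups also lists satisfaction, which is collected only in the intervention group, so it may not promise a comparison. This stands in part: the IMT logs remain valid as a description of how IMT sessions are tolerated.

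Second, safety is to be described, not tested. The t tests are for MIP and the secondary measures, and Textbox 1 sets thresholds only for recruitment and retention. This stands. A reader might infer that the trial carries some false-positive rate for harm. The protocol does not support that, because it contains no between-arm safety test that could give one.

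Third, a reader might infer that there is no comparator for any symptom. That goes too far. The MRC scale, Borg ratings at exercise testing and the qualitative descriptors are taken in both arms at baseline and week 8, so worsening dyspnea has a randomized comparison. It is partial, since it does not count events between visits. Chest discomfort, nausea and soreness have no such matched record. The protocol does not describe nausea as a symptom of the disease.

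Fourth, usual care participants meet staff at the rehabilitation program's week 4 and week 8 sessions and at the study assessments, and an article may leave visit forms to the full protocol. However, this article does set out safety collection in detail and attaches each scheduled element to IMT. Volunteered reports do not match weekly questions, and later analysis cannot recover events that were never asked about.

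**Conclusion.** The concern holds in a limited form. As described, scheduled adverse-event collection covers one randomized arm, while the planned summary refers to the study groups. Any side-by-side rates would be biased towards more events with IMT. The IMT rate for chest discomfort, nausea and soreness would have no like-for-like background rate. Dyspnea is partly protected by the common scales, and the IMT logs still describe tolerability.

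The direction of the bias follows from the design; its size does not. In the first illustration the spurious excess runs from about 4 points (2% per week, three quarters volunteered) to 57 points (10% per week, none volunteered). In the second it runs from about 8 to 40 points. All of this rests on assumed background and reporting rates, and the first illustration also on independence between weeks, which is doubtful for chronic symptoms. These figures are an illustrative range only. The change is worth making because it is cheap and removes the bias at its source.

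**What to change.** - Add one adverse-symptom entry (chest discomfort, worse breathlessness, nausea, muscle soreness, other) to the exercise log that both arms already keep.
- Ask both arms the same symptom question at the existing week 4 and week 8 assessments.
- Base any across-arm adverse-event summary on these common sources only.
- Report events found only through IMT session logs or weekly IMT meetings separately, as IMT-arm tolerability.
- Limit the common-source summary to participants enrolled after the change.

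The cost is a little more log review for the coordinator and an ethics amendment, which Data Management and Quality Assurance requires before any protocol change. No extra staff or visits are needed. Coverage will be incomplete: by January 2023, 4 + 4 = 8 participants had completed and 5 more were enrolled, which left at most 34 − 13 = 21 to enrol under the new log. If the change comes too late to cover a useful number, the report should present adverse events as IMT-arm tolerability only and make no comparison between the arms.

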### Hypotheses

We hypothesize that (1) individuals with hEDS or G-HSD will have lower respiratory muscle strength, higher peripheral airway resistance, lower HRQL, and higher anxiety and depression levels than age- and sex-matched healthy controls and that (2) the delivery of IMT and standard-of-care rehabilitation will be feasible and result in a significant improvement in respiratory muscle strength (MIP) over an 8-week period.

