
#### Primary Pilot Outcome

The primary pilot outcome will be the change in MIP over the 8-week study period to demonstrate the efficacy of IMT, which has been shown to be an important physiological measure in several IMT studies [11,26,35,73].

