##### Objective 2 (Primary Pilot Outcome)

Given an estimated MIP comparable with that of moderate COPD patients (mean 51, SD 15 cm H_2_O), we anticipate a mean increase of 10 (SD 3.5) cm H_2_O in MIP in the IMT and exercise training group compared with the hEDS or G-HSD usual care group (exercise training alone; 5 cm H_2_O) [75]. Assuming a maximum attrition rate of 20% among the 34 RCT participants with hEDS or G-HSD, we will have 90% power (α=.05) to observe a significant difference in MIP with 17 participants per group.

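### The article does not settle whether a within-arm or a between-arm change in MIP decides the primary pilot outcome, and only the between-arm one can show efficacy of IMT

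*Protocol article*

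**What the plan says.** Five places in the protocol article bear on what decides the primary pilot outcome.

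- **Abstract, Methods.** The tests named are "Paired 2-tailed" t "tests will be used to assess the changes in MIP and secondary measures after 8 weeks of IMT". A paired pre-post test is a within-arm test. The abstract names no between-arm test for MIP.
- **Hypotheses.** Hypothesis 2 is that IMT plus standard-of-care rehabilitation will be feasible and "result in a significant improvement in respiratory muscle strength (MIP) over an 8-week period". It names no comparator and no test. Hypothesis 1 does name a comparator, the healthy controls.
- **Primary Pilot Outcome.** The outcome is the "change in MIP over the 8-week study period to demonstrate the efficacy of IMT". Here the change is tied explicitly to the efficacy of IMT, again without a contrast between arms.
- **Proposed Data Analyses, objective 2.** Paired t tests and t tests are to compare changes "over the 8-week study period within and between the 2 randomized groups", and between-group differences are to be reported with 95% CIs. Neither test is given precedence.
- **Sample Size, Objective 2.** "we anticipate a mean increase of 10 (SD 3.5) cm H_2_O in MIP in the IMT and exercise training group", set against the "usual care group (exercise training alone; 5 cm H_2_O"). With up to 20% attrition, "we will have 90% power (α=.05) to observe a significant difference in MIP with 17 participants per group". This calculation concerns a between-arm difference.

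**The concern.** Both randomised arms receive the same rehabilitation programme, and the sample size section expects that programme alone to raise MIP by 5 cm H2O. A significant pre-post rise in the IMT arm is therefore what the plan predicts even if IMT contributes nothing. A reader who follows the abstract, hypothesis 2 and the Primary Pilot Outcome section could take such a rise as confirmation, and under the outcome definition could credit it to IMT. Only the comparison with the randomised usual care arm removes the gain that rehabilitation would have produced anyway. What is at stake is whether the conclusion on the primary pilot outcome uses the randomisation, and whether a pre-post result could be reported as efficacy after the data are in.

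**Working it through.** **Inputs**
- Expected gain with IMT plus rehabilitation: 10 cm H2O, SD 3.5 (Sample Size, Objective 2).
- Expected gain with rehabilitation alone: 5 cm H2O (same section). No SD is given for this arm.
- Two-sided α = 0.05; the abstract says the paired tests are 2-tailed, and two-sided is assumed for the between-arm test.
- 17 per arm with at most 20% attrition: 17 × 0.8 = 13.6, so about 13 to 14 completers per arm.
- Assumption: SD 3.5 is the SD of the change and applies to both arms. SDs of 5 and 8 are added as assumptions to show the range.

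**1. The plan's own sample size**

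The between-arm difference is 10 − 5 = 5.

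n per arm = 2 (1.960 + 1.282)² × 3.5² / 5² = 10.3, so 11; for attrition, 11 / 0.8 = 13.75, so 14.

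With the noncentral t distribution, 11 per arm gives 89.0% power and 12 gives 91.7%, so 12 are needed; 12 / 0.8 = 15. The stated 17 per arm for 90% power is therefore reproduced with a small margin, and it is reproduced as a between-arm calculation.

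**2. The paired test in the IMT arm if IMT adds nothing**

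The IMT arm would then gain only the 5 cm H2O expected from rehabilitation. The paired t statistic has noncentrality 5 / (SD / √n) on n − 1 degrees of freedom.

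- n = 13, SD 3.5: 5 / (3.5 / √13) = 5.15; critical value 2.179; P(significant) = 99.7%.
- n = 17, SD 3.5: 5 / (3.5 / √17) = 5.89; critical value 2.120; P(significant) = 99.98%.

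| SD of change | n = 13 | n = 14 | n = 17 |
|---|---|---|---|
| 3.5 (stated for the IMT arm) | 99.7% | 99.8% | 99.98% |
| 5 (assumed) | 91% | 93% | 97% |
| 8 (assumed) | 54% | 58% | 68% |

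In the same situation a between-arm t test is significant 5% of the time.

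**3. The between-arm test on the plan's inputs**

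Noncentrality = 5 / (3.5 × √(2/n)) on 2n − 2 degrees of freedom.

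- n = 13 per arm: 3.64; power 93.7%.
- n = 17 per arm: 4.16; power 98.1%.

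These depend on the SD: at an assumed SD of 5, power would be 69% with 13 per arm and 81% with 17. That is a question about the sample size inputs. It does not make the paired test a valid substitute.

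**The case against.** The strongest reply is that the randomised comparison is already in the plan. The abstract's Objective and the Study Aims state the comparison with standard-of-care rehabilitation. Proposed Data Analyses lists between-group t tests and CIs, and the sample size was computed for that contrast. Hypothesis 2 names no test and speaks of the combined package, so it does not itself credit the gain to IMT. An abstract condenses, objective 2 is mainly about feasibility, and a ranking of tests might sit in an analysis plan that is not shown.

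Most of this stands, and it limits the point. A reader might infer that the trial as a whole judges IMT by within-arm tests alone, or that its false-positive rate is about 100%. The documents support neither. No passage states that a significant paired test is by itself proof of an IMT effect, and a paired test that detects a true 5 cm H2O gain correctly rejects no change. The error would come in attributing that gain to IMT. A reader might also add a learning effect from repeating the MIP test, but the article gives no statement or figure on this and the argument does not need one. Whether within-arm p values are printed is a reporting preference.

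What the reply does not remove is the disagreement in the current text. The Primary Pilot Outcome section is main text, ties an uncontrolled change to efficacy, and does not match the contrast that the trial was sized for. An unseen analysis plan may rank the tests, but it would not correct the abstract, hypothesis 2 or the outcome definition.

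**Conclusion.** The point holds as an internal inconsistency about what decides the primary pilot outcome. The abstract, hypothesis 2 and the outcome definition frame success as a change over time, the sample size is for a difference between arms, and the analysis section lists both without precedence. On the plan's own expectation for usual care, the within-arm reading cannot show efficacy of IMT: with no IMT effect, the paired test would be significant 99.7% to 99.98% of the time with 13 to 17 completers, 91% to 97% at SD 5 and 54% to 68% at SD 8. These figures assume that the IMT arm would gain exactly the 5 cm H2O expected from rehabilitation. The first range also carries the SD of 3.5, stated only for the IMT arm, over to that gain; the other SDs are assumed. The figures describe a wrong conclusion only if the paired result is read as an effect of IMT, which the wording permits but does not prescribe. The planned analysis is not invalid, because the right test is already listed.

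**What to change.** State in Primary Pilot Outcome and in Proposed Data Analyses that the efficacy of IMT is judged by the between-arm difference in 8-week MIP change, with its 95% CI, as the primary analysis. Name that comparison in the abstract's Methods. Give hypothesis 2 its comparator, for example a greater improvement in MIP than with standard-of-care rehabilitation alone. Describe within-arm changes as descriptive and not as evidence of efficacy.

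The cost is wording only. The test is already listed, the sample size was computed for it, and on the stated inputs no participants need be added. The Results section reports 4 completers per arm as of January 2023 and enrolment continuing to December 2023, so on that timetable the primary contrast could be fixed before data collection ended. In any case it should be documented before the arms are compared.
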